#### In-home preoperative intervention (PRE_EXP2)

The in-home exercise program is essentially based on the same principles than PRE_EXP1, but adapted so it can be conducted at home. The first day is an education with the explanation of the exercises. The training is carried out in the hospital and is supervised by the physiotherapist. The participant is asked to repeat the exercises, and possible doubts are resolved. The intervention consists of a phase with exercises to strengthen the main musculature of the lower limb, and a second phase of balance and proprioceptive work. The muscular enhancement exercises are isometric quadriceps in extension, elevations of the lower limb with knee in extension, ankle in dorsal flexion, and slight hip flexion combined with abduction and adduction. Additionally, the middle gluteal and open chain quadriceps are also performed. Each set of exercises is performed in 4 series consisting of 10 repetitions with a rest of 90 s between each series. The proprioception exercises consisted of tandem position and walking, single-leg position, and treadmill walking. Each exercise has to be performed for 2–4 min. And the participants were asked to do so safely, for instance in a hallway or in front of a table or chair, to avoid falls. After session 6, the participant is appointed for a reminder and verification of exercises, as well as possible corrections in the implementation of the intervention. The participant is requested to register the number of sessions performed in a calendar. The physiotherapist phones the participants on a weekly basis, in order to check both the compliance of the program and the calendar fulfillment.

#### Non-active preoperative intervention (PRE_NA)

In order to evaluate the true effect produced by the interventions, and to determine whether the postoperative results obtained are due to the appropriateness of the proposals, a non-active control group (third arm) was added.

### Reproducibility of the interventions

The procedures were standardized and pilot tested to ensure participant recruitment, outcome evaluation, data handling and management, and safety. A verification of the procedures is planned for periods of 6 months, through observation and meetings to ensure the reproducibility of the protocols and their consistency.

### Outcomes

#### Summary of outcomes and prioritization

In order to characterize de sample and test potential predictors, the sample descriptors and the baseline characterization in terms of the demographic and biomedical characteristics are extracted, including comorbidities.

The following outcome measures are of interest in this trial, according to the proposed hierarchy.
**Primary outcomes**

Self-reported function in daily living as measured with the Knee Injury Osteoarthritis Outcome Score (KOOS) [24].The overall state of balance in terms of the Berg Balance Scale [18].
b.
**Secondary outcomes**

Knee function in terms of the range of motion in flexion and extension and the isometric quadriceps strength.Abilities in terms of dynamic and static balance, as well as testing the limits of stability, as measured with the Timed Up & Go Test, the Single Leg Standing Balance Test, and the Functional Reach Test respectively.Pain, assessed with the Pain subscale of the KOOS scoring system.Quality of life and preoperative anxiety, assessed with the health-related questionnaire the EuroQoL-5D and the corresponding subscale of the KOOS scoring system.
c.

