##### EuroQoL-5D

This is a questionnaire administered to measure the health-related quality of life. The descriptive system contains 5 dimensions of health [27]. It is important to note that preoperative anxiety is being assessed with item number 5 of this test.

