#### Outcome assessment

The baseline assessments will be carried out by a physiotherapist blinded to the interventions, following the signing of an informed consent form and prior to the start of the physiotherapy sessions. The proposed time for the outcome evaluation is in the preoperative period (baseline, between 8 and 4 weeks), before (1 week) and after (2 weeks) the surgical procedure, after the postoperative intervention (6 weeks) and 12 months follow-ups. Details are given in Table 2.

**Table 2 Tab2:** Detail of variables and times for evaluation of outcomes

Time point	Enrolment	BL	BP	AP	AI	12 m
Eligibility screen	x					
Informed consent	x					
Randomization	x					
Assessments						
Demographic and biomedical	x					
Primary						
Self-reported functionality	KOOS	x	x	x	x	x
Balance (overall)	Berg Balance Scale	x	x	x	x	x
Secondary						
Function	ROM (flexion)	x	x	x	x	x
	ROM (extension)	x	x	x	x	x
	Strength	x	x	x	x	x
Balance (dynamic)	Timed Up & Go	x	x	x	x	x
(static)	One-leg Stand	x	x		x	x
(stability)	Functional Reach	x	x	x	x	x
Quality of Life	EuroQoL	x			x	x
Anxiety	EuroQoL(5D)	x	x		x	
Cost-effectiveness						
	Qaly					x
Patient expectations						
		x			x	x
Interventions		BL	BP	AP	AI	12 m
Non-active comparator				x------x		
In-hospital preoperative		x------x		x------x		
In-home preoperative		x------x		x------x		

*BL* Baseline, *BP* Before procedure, *AP* After procedure, *AI* After intervention, *KOOS* Knee Injury Osteoartritis Outcome Score, *ROM* Range of Movement in degrees, *Qaly* Quality adjusted life year

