### Data analysis

The implementation of protocols will be presented with descriptive statistics. In an exploratory way, the drop-out ratios will be estimated and the survival analyses will be used [29]. This aspect will also be taken into account throughout the follow-up and registering when drop-outs occur. The incidence of adverse effects at 6 weeks will be evaluated, which will be categorized according to whether they are considered to be definitive, probable or possibly related to the interventions.

It is hypothesized that the experimental groups will have enhanced balance abilities, which may also have a direct impact on functionality in the short and mid-term. All temporal instants are of interest, although particular attention will be paid to the early postoperative effects (6w) and maintenance of potential mid-term benefits (1y).

The data analysis will include the sample descriptors, a comparison of the baseline condition with the t tests that will be parametric or not depending on the results of the tests of Wilcoxon and Shapiro-Wilk, and a comparison of the progress due to the results of the intervention with an ANOVA analysis of repeated measures, looking for interactions initially as a function of time, group, and time per group. In case of baseline differences between the participants, an ANCOVA analysis will be conducted instead, in which the data will be adjusted to the baseline scores. Analyses will be performed for primary and secondary outcomes. Post-hoc analyses will be performed accordingly. The significance levels will be set at 95%.

A qualitative analysis will be carried out in which it will be estimated if the obtained progressions measured as the mean values of the difference between the basal and final values for each variable at each time point reach the minimum established according to the psychometric properties referring to the minimum clinical importance difference or minimum detectable change with a CI of 95%, if they are available in the literature. If they had been reported by different studies, it would be based on the suggested minimum value.

A post-hoc power analysis and an estimate of the effect size will be implemented with the tool G*Power [20], based on Cohen’s *d* and considering a low, medium or high effect as a function of the result [30].

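### Anxiety is named as a preoperative outcome but is also scheduled 6 weeks after surgery, and no passage ties its conclusion to the before-procedure visit

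*Protocol article*

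**What the plan says.** **Definition.** The Secondary outcomes list of the protocol article gives "Quality of life and preoperative anxiety, assessed with the health-related questionnaire the EuroQoL-5D". The EuroQoL-5D section, under Outcomes description, repeats the restriction: "preoperative anxiety is being assessed with item number 5 of this test".

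**Schedule.** Table 2 (Outcome assessment) has its own Anxiety row, with the instrument EuroQoL(5D). It is marked at baseline (BL), before the procedure (BP) and after the intervention (AI), and is blank after the procedure (AP) and at 12 months. The text fixes the timing of BP and AP as "before (1 week) and after (2 weeks) the surgical procedure" and of the last two visits as "after the postoperative intervention (6 weeks) and 12 months follow-ups". A separate Quality of Life row schedules the full EuroQoL at BL, AI and 12 months.

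**Analysis.** The Data analysis section plans an "ANOVA analysis of repeated measures, looking for interactions initially as a function of time, group, and time per group". It replaces this with a baseline-adjusted ANCOVA only if the groups differ at baseline. On scope it says "Analyses will be performed for primary and secondary outcomes", followed by "Post-hoc analyses will be performed accordingly". On visits it says "All temporal instants are of interest, although particular attention will be paid to the early postoperative effects (6w" weeks) and the maintenance of benefit at one year.

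**The concern.** The three statements do not fit together. The name restricts the outcome to the period before surgery. The schedule includes a score taken after surgery and after the postoperative programme. The analysis section describes one method for all outcomes and exempts none.

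Only one assessment lies after the preoperative training and before surgery, namely BP. Baseline is also preoperative, but training cannot yet have affected it. The one contrast that answers the question in the outcome's name is therefore BP given baseline. A time-by-group test over BL, BP and AI asks something wider: whether the arms' profiles differ anywhere across the three visits. A difference that arises only at 6 weeks can make it significant.

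What is at stake is the interpretation of one secondary result. A reader who sees a significant interaction under the heading of preoperative anxiety could not tell from that test whether anxiety differed before surgery.

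**Working it through.** The documents give no effect size, standard deviation, correlation or power for anxiety, so there is no stated figure to reproduce. The check has two parts.

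**1. Table alignment.** Header and Anxiety row have seven cells each. Set side by side, the marks fall under BL, BP and AI, so the 6-week mark is not caused by shifted columns.

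**2. What each test responds to.**

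Inputs from the Sample size section: three equal arms, n = 20 per arm after loss (25 recruited), α = 0.05. Assumptions: normal scores with SD 1, equal correlation ρ = 0.5 between visits, and both trained arms differing from control by d at a single visit.

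The noncentrality parameter λ follows from the pattern of means. Across arms (0, d, d), the squared deviations sum to (2/3)d². For an effect at one visit, the squared visit deviations sum to 2/3 with three visits and 1/2 with two.

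- Three-visit interaction: λ = n·(2/3)(2/3)d²/(1−ρ), with 4 and 114 df
- BL/BP-only interaction: λ = n·(2/3)(1/2)d²/(1−ρ), with 2 and 57 df
- ANCOVA of BP on BL: λ = n·(2/3)d²/(1−ρ²), with 2 and 56 df

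*Difference of 0.8 SD at 6 weeks only, none before surgery.* For the three-visit interaction, λ = 20 × 0.4444 × 0.64/0.5 = 11.38. Noncentral F gives 76%, and simulation gives 75% to 76%. The two tests that use only BL and BP have λ = 0 and reject at the nominal 5%.

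The range for the three-visit test with a 6-week-only difference and ρ from 0.5 to 0.7 (3,000 simulated trials each) is:

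| Per arm | 0.5 SD | 0.8 SD |
|---|---|---|
| 20 | 35% to 55% | 75% to 94% |
| 25 | 43% to 65% | 86% to 98% |

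With no difference at any visit, all tests reject in about 5%. Item 5 is a single item. With scores cut into three ordered levels (assumed cut points) and 20 per arm, the 0.8 SD scenario gives 59% against 5%, so the mechanism remains.

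*True effect at BP only, gone by 6 weeks (20 per arm, ρ = 0.5).* At 0.6 SD:

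- Three-visit interaction: λ = 20 × 0.4444 × 0.36/0.5 = 6.4, power 48%
- BL/BP-only interaction: λ = 20 × 0.3333 × 0.36/0.5 = 4.8, power 47%
- ANCOVA of BP on BL: λ = 20 × 0.6667 × 0.36/0.75 = 6.4, power 59%

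Simulations agree within one or two points (about 47%, 45% to 46%, and 57% to 58%). At 0.8 SD the calculated values are 76%, 72% and 84%. Removing the 6-week score alone gains no power and costs a little. The gain comes entirely from adjusting for baseline.

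**The case against.** Several points on the other side are sound.

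- **The plan has ways to locate a 6-week-only difference.** The interaction is only the initial step. Post-hoc tests follow, and progress is judged for each variable at each time point against published minimum differences. A reader might infer that a purely postoperative difference would be reported as an effect on preoperative anxiety. The documents do not support that: it would also require the authors to disregard these later steps. What remains is that no passage makes the BP result the basis for the preoperative claim.
- **The visits in the anxiety model are inferred.** The section describes one general approach and does not list visits by outcome. Pooling BL, BP and AI is the natural reading but is not stated for anxiety by name. Detail of that kind may properly sit in a fuller plan. The mismatch between name and schedule does not depend on it, since both are in this article.
- **The 75% against 5% contrast follows largely from its construction.** A difference is placed at one visit, and only the test that includes that visit can see it. It shows what the test responds to, not how likely such a pattern is. The documents give no reason to expect anxiety to be unchanged before surgery yet different six weeks later.
- **The AI mark has an innocent explanation.** The full EuroQoL is collected at AI anyway. What the Anxiety row adds is the BP assessment, and Table 2 labels the row simply as anxiety. A reader might take the blank at 12 months as lost data, but item 5 is collected there within the full EuroQoL.
- **A reader might infer that the 6-week score dilutes power.** The calculation above shows that it does not.

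**Conclusion.** The point holds as an inconsistency between definition, schedule and analysis. Anxiety is twice called preoperative, is also scheduled 6 weeks after surgery, and falls under a general time-by-group test that does not isolate the before-procedure visit. Under the assumptions stated (normal scores, 20 per arm, correlation 0.5, a 0.8 SD difference only at 6 weeks), that test is significant in about 75% of trials although nothing differs before surgery. Effect sizes and correlation are illustrative and do not come from the documents.

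The point does not establish that a misreport would occur, or that the 6-week score weakens the test. Its importance is minor: it concerns one single-item secondary outcome, and the primary outcomes are unaffected.

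**What to change.** 1. In the Secondary outcomes list and the EuroQoL-5D section, define preoperative anxiety as item 5 at the before-procedure visit.
2. In Data analysis, state that arms are compared on that score by ANCOVA adjusted for baseline item 5, whether or not the arms differ at baseline. The adjustment raises power from about 45% to 47% to about 58% at 0.6 SD under the assumptions above.
3. In Table 2, label the 6-week score as a separate postoperative anxiety outcome, together with the 12-month item already collected within the full EuroQoL.

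The cost is a few words in the outcome sections, one label in Table 2 and one separate model for this outcome. No data are added or lost.

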**Other outcomes**

Economic evaluation. Cost-effectiveness analysis.Qualitative evaluation: Patient expectations and caregivers opinion.

#### Outcomes description

**KOOS** is a self-reported questionnaire developed as an instrument to assess the patient’s opinion about their knee and associated problems. It evaluates the short-term and long-term symptoms and function in subjects with knee injury and osteoarthritis. The KOOS holds five separately scored subscales: Pain, other Symptoms, Function in daily living (ADL), Function in Sport and Recreation (Sport/Rec), and knee-related Quality of Life (QOL). A normalized score is calculated for each subscale, being 100 no symptoms and 0 extreme symptoms [24]. All subscales are evaluated in this research, but Sport/Rec. The ADL scale is set as primary outcome, together with the Berg Balance Scale. All other scales are considered secondary outcomes.

The **Berg Balance Scale**, is used to assess balance abilities in terms of the overall state of balance. It is a 14-item questionnaire administered in order to measure balance among older people with impairment in the balance function by assessing the performance of functional tasks [18].

The **Timed Up & Go Test,** used to assess dynamic balance, is a test of general mobility, in which the individual rises from a standard arm chair without using their arms, walks 3 m, turns around, returns to the chair, and sits down [25]. The test score measured in seconds is taken as the mean of 2 trials.

The **Single Leg Standing Balance Test** is a simple method to assess static balance. It measures the time that a patient can hold their balance on just one leg. This outcome could not be assessed after the procedure, due to the medical prescription, since it is too early to achieve one-legged support.

The **Functional Reach Test**, used to assess stability, is a test to detect balance deterioration and changes in performance over time, measures the maximum distance the participant could reach forward while standing in a fixed position. The procedures are adapted based on those described by Duncan [26].

##### Knee function range of movement (ROM)

The joint function in terms of flexion and extension range of movement will be measured with a manual goniometer. The participants are placed in a supine position while the hip was bended at 90 degrees.

##### Knee function strength

For the measurement of the strength of the quadriceps, a dynamometer Manual Muscle Tester 01165 Lafayette Instrument® is used. The isometric force of both quadriceps is measured for 6 s. The test is performed 3 times and the mean is calculated. The maximum peak force data are also extracted.

##### EuroQoL-5D

This is a questionnaire administered to measure the health-related quality of life. The descriptive system contains 5 dimensions of health [27]. It is important to note that preoperative anxiety is being assessed with item number 5 of this test.

##### Pain

This will be assessed with the Pain subscale of the KOOS scoring system [28].

#### Other outcomes

##### Qualitative evaluation of patient expectations

The evaluation will be based on the anchor methods, asking the participant about their expectations of the benefits that they hope to achieve due to the surgical intervention and following their participation in the trial. The questions will be answered with a Likert scale. Subsequently, the fulfillment of these expectations will be verified.

##### Economic evaluation

Cost-effectiveness analysis, which is further explained in the data analysis section.

#### Outcome assessment

The baseline assessments will be carried out by a physiotherapist blinded to the interventions, following the signing of an informed consent form and prior to the start of the physiotherapy sessions. The proposed time for the outcome evaluation is in the preoperative period (baseline, between 8 and 4 weeks), before (1 week) and after (2 weeks) the surgical procedure, after the postoperative intervention (6 weeks) and 12 months follow-ups. Details are given in Table 2.

**Table 2 Tab2:** Detail of variables and times for evaluation of outcomes

Time point	Enrolment	BL	BP	AP	AI	12 m
Eligibility screen	x					
Informed consent	x					
Randomization	x					
Assessments						
Demographic and biomedical	x					
Primary						
Self-reported functionality	KOOS	x	x	x	x	x
Balance (overall)	Berg Balance Scale	x	x	x	x	x
Secondary						
Function	ROM (flexion)	x	x	x	x	x
	ROM (extension)	x	x	x	x	x
	Strength	x	x	x	x	x
Balance (dynamic)	Timed Up & Go	x	x	x	x	x
(static)	One-leg Stand	x	x		x	x
(stability)	Functional Reach	x	x	x	x	x
Quality of Life	EuroQoL	x			x	x
Anxiety	EuroQoL(5D)	x	x		x	
Cost-effectiveness						
	Qaly					x
Patient expectations						
		x			x	x
Interventions		BL	BP	AP	AI	12 m
Non-active comparator				x------x		
In-hospital preoperative		x------x		x------x		
In-home preoperative		x------x		x------x		

*BL* Baseline, *BP* Before procedure, *AP* After procedure, *AI* After intervention, *KOOS* Knee Injury Osteoartritis Outcome Score, *ROM* Range of Movement in degrees, *Qaly* Quality adjusted life year

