### Blinding and randomization

Participation occurs sequentially. At the time that a subject has an established date of operation, the physician checks the criteria are being met. If so, the potential participant is informed of the study and is referred to the rehabilitation department where, if is definitely admitted will take part in the randomization process. The randomization is generated from the output of the Matlab® statistical program by external assessor. A physiotherapist with 3 years of experience and blinded to the intervention groups will be in charge of the outcome assessment. The blinding of the participants is not assured, as they are informed about the trial before randomization. Neither is it the blinding of those who provide the treatments for the same reason. However, physiotherapists do not take part in the process of randomization and participant allocation. The external assessor in charge of the randomization is blinded to the intervention groups that have a numerical coding, and will receive the data of the participants for the statistical processing. The interpretation of the results will be carried out by the whole team.

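### Randomisation is scheduled before baseline and nothing requires baseline to be finished before the arm is known, so self-reported baseline scores may be given with knowledge of allocation

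*Protocol article*

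**What the plan says.** Three parts of the protocol article bear on the order of steps.

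- **Table 2 (Outcome assessment).** "Randomization" is ticked in the Enrolment column, with the eligibility screen and consent. KOOS and Berg are first ticked in the next, separate column, BL.
- **Blinding and randomization.** The patient is referred to the rehabilitation department and "if is definitely admitted will take part in the randomization process". No baseline step is placed before this. The same section adds: "The blinding of the participants is not assured, as they are informed about the trial before randomization".
- **Outcome assessment, text.** "The baseline assessments will be carried out by a physiotherapist blinded to the interventions", with the timing given as "following the signing of an informed consent form and prior to the start of the physiotherapy sessions", between 8 and 4 weeks before surgery. Randomisation is not named as a boundary.

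KOOS-ADL is a self-reported co-primary outcome. The other co-primary is "The overall state of balance in terms of the Berg Balance Scale", which is scored on task performance.

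The Data analysis section uses baseline in four ways: in the baseline comparison between groups, in the repeated-measures ANOVA (time by group), in an ANCOVA "in which the data will be adjusted to the baseline scores" if baseline differences are found, and in the mean change from baseline set against published minimum important or detectable differences.

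**The concern.** A baseline value is a safe reference because allocation cannot have affected it. That holds when it is taken before randomisation, or at least before the participant learns the arm. Here the schedule puts randomisation first, and the only later limit on baseline is the first physiotherapy session. For the non-active arm that limit is weak, since Table 2 shows no preoperative sessions in that arm.

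The arms are supervised hospital training, home training and no preoperative training, so allocation is obvious once disclosed. A participant who has just learned the arm may rate function, anxiety or expected benefit differently. A blinded assessor cannot protect a score that the participant supplies.

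If such a shift differs between arms, the baseline is no longer independent of treatment. Change-based contrasts then carry the shift, ANCOVA carries part of it, and the test that decides between ANOVA and ANCOVA can be triggered by it.

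**Working it through.** **Order of steps.** Set side by side:

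1. Table 2: screen, consent and randomisation at Enrolment, then KOOS at BL.
2. Blinding and randomization: admission, then randomisation; baseline is not mentioned.
3. Outcome assessment text: consent, then baseline, then sessions; randomisation is not mentioned.

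Items 1 and 2 agree. Item 3 is compatible with baseline on either side of randomisation. No sentence places baseline first, and none says when the arm is disclosed.

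**Bias.** The documents give no figure for a reporting shift, so what follows is algebra and an assumed range. For one arm against another, let:

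- τ = the true effect at follow-up
- b = the differential shift in the baseline score caused by knowing the arm
- s = the differential reporting shift at follow-up
- β = the slope of follow-up on baseline

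| Analysis | Expected contrast | Bias if s = 0 | Bias if s = b |
|---|---|---|---|
| Change, or baseline-to-visit interaction | τ + s − b | −b | 0 |
| ANCOVA on baseline | τ + s − βb | −βb | (1 − β)b |
| Follow-up score alone | τ + s | 0 | b |

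With b = 0 and s = 0 no analysis is biased.

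**Illustration for s = 0, in SD units.** The article gives no KOOS standard deviation. The group size comes from Sample size: 20 evaluable per arm (3 × 20 = 60; 60 / 0.80 = 75, the stated total). The values of b and of the baseline–follow-up correlation ρ are assumptions. With equal variances β = ρ.

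- Standard error, change: √(2(1 − ρ) × 2/20). At ρ = 0.5 this is √0.10 = 0.316.
- Standard error, ANCOVA: √((1 − ρ²) × 2/20). At ρ = 0.5 this is √0.075 = 0.274.
- Type I error: Φ(−1.96 − |bias|/SE) + 1 − Φ(1.96 − |bias|/SE).

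At ρ = 0.5:

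| b (SD) | Change: size of bias, type I error | ANCOVA: size of bias, type I error |
|---|---|---|
| 0 | 0, 0.05 | 0, 0.05 |
| 0.1 | 0.10, 0.062 | 0.05, 0.054 |
| 0.2 | 0.20, 0.097 | 0.10, 0.065 |
| 0.3 | 0.30, 0.158 | 0.15, 0.085 |
| 0.5 | 0.50, 0.353 | 0.25, 0.150 |

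Over b = 0.1 to 0.5 and ρ = 0.3 to 0.7, type I error for a two-arm contrast runs from 0.058 to 0.53 for change and from 0.051 to 0.34 for ANCOVA.

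**The ANCOVA trigger.** A two-arm baseline comparison has standard error √(2/20) = 0.316, the same as the change score at ρ = 0.5. A shift of 0.2 SD would therefore make it significant about 10% of the time instead of 5%.

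The bias does not depend on sample size, so more participants would not reduce it.

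**The case against.** **Disclosure before baseline is not documented.** A reader might infer that participants know their arm when they complete the baseline KOOS. The article does not say so. The reason it gives for non-blinding is that participants hear about the trial before randomisation, not that the arm is released before baseline. Consent, baseline, then disclosure would also fit the text. This stands: the plan permits the problem but does not show that it happens.

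**Table 2 may be a loose record of order.** The eligibility Berg is not ticked at Enrolment, and instrument names occupy that column in the assessment rows. A condensed article may also leave the order of steps at a visit to the full protocol. This stands only in part. The table does more than omit an order: it puts randomisation in an earlier column than baseline, and the text on randomisation agrees with it.

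**Not every baseline-referenced comparison is exposed.** A reader might extend the point to all outcomes. Berg, Timed Up & Go, Functional Reach, range of motion and strength are measured by a blinded physiotherapist. For these, only the effort of an unblinded participant could matter, and nothing in the documents gives that a size.

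**The size depends on what happens at follow-up.** Participants remain unblinded. If the same reporting shift persists, it cancels in the change score, so it is not generally true that using this baseline adds bias. This stands, and it is why no single figure should be quoted.

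**Conclusion.** The point holds as a risk that the written schedule permits, confined mainly to self-reported measures: KOOS-ADL as co-primary, the other KOOS subscales, EuroQoL including its anxiety item, and expectations.

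The documents do not support saying that these baselines are biased, that every comparison is affected, or that the bias is a given number of KOOS points. Each would need a disclosure time or a shift that the article does not give.

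The size is unknown, from nil to material. If a differential shift b affects baseline only, the bias is −b for change scores and −slope × b for ANCOVA. At an assumed 0.2 SD with correlation 0.5 and 20 per arm, a nominal 5% two-arm test would have a type I error of about 10% (change) or 6.5% (ANCOVA). With b = 0 there is no bias. The point deserves action because the remedy is specific and cheap.

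**What to change.** **Order.** State it as eligibility, consent, all baseline assessments, then randomisation and disclosure of the arm. Move randomisation in Table 2 to after BL, and say the same under Blinding and randomization and under Outcome assessment. If baseline already comes first in practice, correcting the table and text is enough.

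**Participants already enrolled.** Record for each whether baseline KOOS came before or after the arm was disclosed. Report a sensitivity analysis of follow-up scores without baseline adjustment. It is free of any baseline shift, though not of a reporting shift at follow-up. Its standard error at ρ = 0.5 is 0.316 SD against 0.274 SD for ANCOVA, about 15% larger.

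**Avoid.** Do not substitute the eligibility Berg for the blinded baseline Berg. It is scored by different staff at a different time, and it does nothing for KOOS.

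**Cost.** No assessment is added, and allocation is released slightly later. Recruitment began in March 2017 and was expected to end by June 2018, so a change in mid-recruitment reaches only later participants and leaves a mixed baseline order, which should be reported.
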